#### **b.Secondary outcomes**

The secondary outcomes of the study will assess the effect of the intervention on the adolescents living with HIV at the intervention facility. A cross-sectional survey and physiological assessments will be conducted among 20 randomly selected adolescents per facility at baseline and six months after the intervention in both arms of the study.

1. **Cross-sectional Survey among Adolescents Living with HIV**

This survey will validate the data extracted from the records and confirm that the adolescents received the interventions. Data will be collected by face-to-face interviews using a structured questionnaire based on an adaption of the WHO STEPS Questionnaire for Chronic Disease Risk Factor Surveillance(WHO, 2012). The questionnaire will collect data on; socio-demographic characteristics, history of tobacco use and alcohol consumption, physical activity, diet and anthropometric measurements. In addition, data will be collected to assess the

- Number of clients who reported having their BPs checked during the last clinical visit
- Number of clients who reported being educated on hypertension and its risk reduction during the last clinical visit and
- The number of clients who reported adhering to any preventive measures (diet, physical activity) in the week prior to the interview.

Height and weight measurements of respondents will be taken with calibrated stadiometers and a weighing scale, respectively. All measurements will be taken using the US Centers for Disease Control and Prevention (CDC) standard procedure(CDC, 2014).

1. **Physiological Assessments**

These assessments will identify adolescents with normal blood pressure, masked hypertension, white coat hypertension, elevated BP and high BP as defined in the guideline for screening and managing hypertension among children and adolescents(Flynn et al., 2017). The assessment will also help identify those at risk of being hypertensive (having arterial stiffness). These will be achieved by measuring their office blood pressure, ambulatory blood pressure and cardio-ankle vascular index (arterial stiffness) as described below.

- **Office Blood pressure**

Participants’ blood pressure will be assessed as recommended in the guideline for screening and managing hypertension among children and adolescents(Flynn et al., 2017) and described in section **2.6.3.**

- **Ambulatory blood pressure measurement(ABPM)**

This will be performed using the CONTEC ABPM50 24H Ambulatory Blood Pressure Monitor. It will be done over 24 h, with BP readings every 30 min. A minimum of 70% accurate readings will be considered sufficient. Wake and sleep periods will be based on sleep and wake times recorded in the participant’s journal. Height-specific ABPM percentiles presented in the guidelines(Flynn et al., 2017) and associated references will be used to define ABPM abnormal BP threshold values and percentiles and to define ABPM-specific BP abnormalities(Fredric et al., 2021).

- **Cardio-Ankle Vascular Index**

This will be assessed using the VaSera 1500N vascular screening system (Fukuda Denshi Co.). As recommended, examinations will be conducted under standard conditions (room temperature 22 °C, minimization of stimuli) between 8.00 and 10.00 a.m. Participants will be instructed to avoid physical exercise and consumption of substances that could affect cardiovascular function (e.g., caffeine, alcohol) 24 hours prior to the examination. Before the examination, participants will rest in a supine position for 15 minutes to avoid the potential effects of stress. At the time of examination, subjects will remain supine with both arms on the bed, parallel to the body, and limb cushions placed below the elbows and heels to prevent contact of the limb cuffs with the bed. Electrocardiographic electrodes will be placed on both wrists, oscillometric blood pressure (BP) cuffs wrapped around the arms and ankles, and a microphone for phonocardiography placed on the sternum at the level of the second intercostal space. The cardio-ankle vascular index will be measured to determine the presence of arterial stiffness based on age- and sex-defined cut-offs(Rico Martín et al., 2020).

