# **Study Summary**

**Background:** Recent studies have shown a relatively higher incidence of cardiovascular diseases and related deaths among persons living with HIV than uninfected persons. The adverse effects of some antiretroviral medication, chronic vascular inflammation, and immune activation from persistent HIV replication leading to arterial stiffness contribute to this. The duration of exposure to the virus plays a vital role in the pathogenesis, putting perinatally infected children and adolescents at higher risk than behaviorally-infected individuals. This, therefore, supports the calls for increased surveillance of NCDs, especially hypertension among them.

**Aim and objectives:** The overall aim of the study is to improve the adherence of healthcare workers to the guidelines for screening and management of hypertension among adolescents living with HIV(ADLHIV) at selected ART sites in the Greater Accra Region. The objectives are to

1. Determine the factors influencing health care workers' adherence to the guidelines for screening and management of hypertension among ADLHIV.
2. Assess the effect of a Theory of Planned Behavior-based intervention on healthcare workers' adherence to guidelines for screening & management of hypertension among ADLHIV.
3. Assess the effect of a Theory of Planned Behavior-based intervention on the arterial stiffness and blood pressure of ADLHIV.

**Methodology:** The study will be conducted among 24 antiretroviral therapy sites in the Greater Accra Region. An elicitation study will be conducted to develop a theory of planned behavior-based questionnaire. This will be used in a survey to determine the factors influencing healthcare workers' intention to check the blood pressure of adolescents living with HIV. A cluster-randomized study will be conducted to assess the effect of a theory of planned behavior-based intervention on healthcare worker adherence to the guidelines as well as the blood pressure and arterial stiffness of adolescents living with HIV after a six-month follow-up period.

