### **2.6.3 Diagnosis of hypertension**

The guideline defined hypertension in children and adolescents as systolic BP (SBP) or diastolic BP (DBP) or both SBP and DBP, which is, on repeated measurement, at or above the 95th percentile for age, sex and height. BP between the 90th and 95th percentile in childhood was designated "prehypertensive".

It further recommended that

1. “BP should be measured in the right arm with an appropriate cuff size(Flynn et al., 2017).
2. Appropriate steps should be taken to ensure the child is comfortable and still for at least 5 minutes prior to measurement.
3. Home BP measurements may help monitor hypertensives but not diagnose new cases.
4. Although measurement with an automatic BP cuff (oscillation device) may be used to screen for elevated BP in the primary care setting, it should be repeated with auscultation if the BP reading is elevated.
5. If an auscultated BP measurement is elevated despite correct measurement technique, it should be repeated two more times at the same visit and the average of the last two auscultatory readings used as a final BP. The degree of elevation should be assessed based on this average with reference to normative BP values for age, sex and height and the revised hypertensive categories as outlined in Figure 2A (Flynn et al., 2017).
6. A diagnosis of paediatric hypertension can be made if the BP remains at or above stage 1 hypertension on three separate clinic visits (Flynn et al., 2017). The timeline for these follow-up BP assessments is as outlined in figure 2A.
7. Compared to adults, their report gave no strict BP cut-off for a hypertensive crisis in children. However, it stated that severe hypertension warranting assessment in the emergency department depends on clinical symptoms, including irritability, headache, oedema, visual changes, or severe abdominal pain(Chandar & Zilleruelo, 2012; N. H. Patel et al., 2012; Stein & Ferguson, 2016).
8. Due to its superiority over isolated BP measurement in diagnosing hypertension and its ability to identify some secondary causes of hypertension, ambulatory blood pressure monitoring (ABPM) was recommended for screening or in confirming the diagnosis of hypertension if
   1. BP remains in the elevated BP category for ≥1 year
   2. BP remains in stage 1 hypertension category over three successive visits.
   3. The patient has high-risk conditions for hypertension (i.e., CKD, diabetes, obesity, or prematurity)

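### Office BP (a secondary outcome) is repeated and averaged only after an elevated reading, which understates the elevated share and costs some sensitivity, without favouring either arm

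*Protocol*

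**What the plan says.** Under Secondary outcomes (protocol section 3.3.9b), office BP is one of three physiological assessments. The text says that participants' "blood pressure will be assessed as recommended in the guideline for screening and managing hypertension among children and adolescents" and refers the reader to section 2.6.3 for the procedure. That section sets out these steps:

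- As an optional start, "measurement with an automatic BP cuff (oscillation device) may be used to screen for elevated BP in the primary care setting". After such a reading, "it should be repeated with auscultation if the BP reading is elevated".
- "If an auscultated BP measurement is elevated despite correct measurement technique, it should be repeated two more times at the same visit", with "the average of the last two auscultatory readings used as a final BP".
- Neither section states a repeat or an average after a normal first reading.

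The result is used for classification: "These assessments will identify adolescents with normal blood pressure, masked hypertension, white coat hypertension, elevated BP and high BP". It is collected in "20 randomly selected adolescents per facility at baseline and six months after the intervention in both arms of the study". Objective 3 in the Study Summary also makes BP an outcome: "Assess the effect of a Theory of Planned Behavior-based intervention on the arterial stiffness and blood pressure of ADLHIV". Objective 3 in section 1.9, research question 4 and hypothesis 2 name arterial stiffness only. Section 3.4.2 plans t-tests or ANOVA for means and a z-test for proportions.

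**The concern.** The sequence suits case finding. Used as an outcome measurement, it makes the number of readings, the averaging and possibly the device depend on the value being measured. A first reading that is high by chance is checked and often brought down. One that is low by chance stands. An adolescent whose usual pressure is above the cut-off but whose single reading fell below it is recorded as office-normal, and as masked hypertension if ambulatory BP is high. The masked and white coat categories therefore move with the office rule even though ambulatory monitoring is done uniformly.

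Three results are at stake: the reported share with elevated or high BP, the split between the office/ambulatory categories, and the ability to detect an arm difference on the absolute scales that section 3.4.2 tests. This is a data-collection rule, so a later analysis plan cannot recover readings that were never taken.

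**Working it through.** **The plan's own figure.** The protocol gives no sample size, SD or expected effect for office BP. Its only calculation (section 3.3.5) is for the primary outcome, and it reproduces: 17% vs 34% at 80% power needs 103 per arm; the design effect is 1 + 19 × 0.05 = 1.95; 103 × 1.95 = 200.9, against 200 for ten facilities of 20.

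**Direction, without assumptions.** Let Y1 be the first auscultated reading, M the mean of the next two, and c the cut-off. Under 2.6.3, elevated means Y1 ≥ c and M ≥ c. Under uniform averaging it means M ≥ c. The first event is contained in the second, so the share under 2.6.3 is equal or lower whatever the SDs. An oscillometric first step adds a third condition and can only lower it further.

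**Size, with assumptions.**
- From the protocol (section 2.4.1, pooled African data, ages 2-19): 5.5% elevated plus 12.7% slightly elevated = 18.2%, taken here as the share of first readings at or above c.
- Assumed, not in the protocol: mean SBP 110 mmHg, between-person SD 10, within-visit reading SD s = 5, 6 or 8, no device offset, no first-reading rise, and 107 mmHg in the other arm (a true 3 mmHg difference).

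Cut-off: c − 110 = 0.908 × √(100 + s²) = 10.15, 10.59, 11.63 mmHg.

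Uniform averaging: P(Z ≥ (c − 110)/√(100 + s²/2)), with arguments 10.15/10.61 = 0.957, 10.59/10.86 = 0.975 and 11.63/11.49 = 1.012, gives 16.9%, 16.5%, 15.6%.

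Usual pressure at or above c: P(Z ≥ (c − 110)/10) = 15.5%, 14.5%, 12.2%.

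The 2.6.3 sequence, simulated with 2,000,000 adolescents per arm:

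| Quantity (s = 5 / 6 / 8) | Uniform averaging | 2.6.3, auscultation only | 2.6.3, oscillometric first |
|---|---|---|---|
| Elevated or higher, % | 16.9 / 16.5 / 15.6 | 11.8 / 10.7 / 8.8 | about 9.2 / 8.0 / 5.9 |
| Arm difference, points | 6.1 / 6.0 / 5.4 | 4.7 / 4.3 / 3.5 | 3.9 / 3.4 / 2.5 |
| True 3 mmHg reads as | 3.0 | 2.9 to 2.7 | 2.8 to 2.6 |
| Standardised mean difference | 0.284 / 0.276 / 0.262 | 0.272 / 0.260 / 0.238 | 0.271 / 0.258 / 0.233 |

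Loss in standardised difference: 1 − 0.272/0.284 = 4% at the smallest, 1 − 0.233/0.262 = 11% at the largest.

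Prevalence ratio (107 vs 110 mmHg arm, s = 5): 0.60 with auscultation only, 0.58 with an oscillometric first step, 0.64 with uniform averaging, 0.61 for usual pressure. It does not move towards 1.

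**Power, for illustration.** With 12 facilities of 20 per arm, ICC 0.05 carried over to BP, s = 5 and a cut-off of 120 mmHg, the effective size is 240/1.95 = 123 per arm. Power for proportions is 29% with uniform averaging against 24% (auscultation only) or 22% (oscillometric first). For means it is 61% against 56%.

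**The case against.** The strongest reply is that section 3.3.9b uses office BP to classify adolescents as the guideline defines the categories, so following the guideline's reading rule is correct by definition, and understatement exists only against a comparator the protocol never chose. No section defines mean office BP as an endpoint, and only the Summary names BP in the objective. Ambulatory BP supplies a uniform measure anyway. The single reading after a normal value is also inferred from silence, which a measurement manual could fill.

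Much of this stands. It makes the point one about a secondary outcome, and it limits what can be said about means. It does not remove the asymmetry: the categories are compared between arms and rounds, two of them combine office with ambulatory readings, and the only procedure the protocol points to repeats selectively.

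A reader might go further and infer any of the following, which the documents do not support:

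- *That the arm comparison is biased in favour of one arm.* The same rule applies in both arms and rounds, and section 3.3.6 keeps outcome assessors blind.
- *That both arms are pulled towards the cut-off.* In this model they lie below it and move away: the 110 mmHg arm falls to 109.4 (auscultation only) or 109.2 (oscillometric first) at s = 5.
- *That mean BP always falls.* With no offset it drops by 0.6 to 1.3 mmHg (auscultation only) or 0.8 to 1.8 (oscillometric first). If first readings run high, it can rise instead.
- *That the test on means is badly weakened.* The rule shrinks the SD as well as the difference.
- *That analysing the first reading alone would cure it.* Its standardised difference is 0.270/0.258/0.235, practically that of the 2.6.3 sequence, and it classes 18.2% as elevated when usual pressure gives 15.5/14.5/12.2%.

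**Conclusion.** The point holds as a measurement defect in a secondary outcome. The direction of the prevalence effect is certain relative to uniform averaging; its size depends on assumptions. In the scenarios above, the elevated share falls by 16.9 − 11.8 = 5.1 to 15.6 − 8.8 = 6.8 percentage points with auscultation only, and the absolute arm difference in proportions by 1.4 to 1.9 points. The loss for means is small.

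Uniform averaging is not error-free either: it lies 1.4 to 3.4 points above the share based on usual pressure, while the auscultation-only sequence lies 3.4 to 3.8 points below. At reading SD 8 the two are about equally far off. The case for uniform averaging is therefore that everyone is measured alike and that it preserves more of the arm difference, not that it returns the exact prevalence.

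The figures use SBP alone, although the protocol classifies on SBP or DBP. The 18.2% comes from general-population data, and its 12.7% component has a confidence interval of 2.1 to 30.4. The primary outcome, the ambulatory readings and the arterial stiffness measure do not use this sequence. This should be corrected before baseline measurement, but it does not threaten the trial's main conclusion.

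**What to change.** Add one sentence to section 3.3.9b, limited to the research outcome: every adolescent has office BP taken with the same device, the same number of readings and the same averaging at baseline and six months, whatever the first value (for example, three readings with the mean of the last two analysed). Name the 24-hour ambulatory mean as the supporting arm comparison; those data are already planned. Do not rely on the first reading alone. Leave the 2.6.3 sequence unchanged for individual clinical follow-up, and say that it is separate from the outcome measurement.

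The cost is protocol wording and a few extra minutes per adolescent per round. The sentence must be in place before baseline so that both rounds are measured alike.

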# **5.0 Appendix**

## **Appendix II: Questions for elicitation study**

Your patient is an adolescent (10-17 years) living with HIV. The target behaviour is measuring the patient’s blood pressure (BP). Please take a few minutes to list your thoughts about the following questions:

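### The ABPM acceptance rule sets no minimum for the sleep period, so a recording with few sleep readings can count as sufficient although it is split into wake and sleep and used to classify BP

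*Protocol*

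**What the plan says.** ABPM is one of three physiological assessments under secondary outcomes (Protocol 3.3.9 b), made at baseline and at six months in both arms. On the schedule: "It will be done over 24 h, with BP readings every 30 min". On acceptance: "A minimum of 70% accurate readings will be considered sufficient". On the division of the recording: "Wake and sleep periods will be based on sleep and wake times recorded in the participant’s journal". Height-specific percentiles from the cited guideline and associated references "will be used to define ABPM abnormal BP threshold values and percentiles and to define ABPM-specific BP abnormalities". The introduction to the physiological assessments gives the purpose: "These assessments will identify adolescents with normal blood pressure, masked hypertension, white coat hypertension, elevated BP and high BP".

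Neither 3.4.1 (data quality control) nor 3.4.2 (data analysis) adds a validity criterion for ABPM, so the overall 70% is the only one in the document. The protocol does not say whether the percentage is taken of scheduled or of attempted readings.

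**The concern.** The rule and the use of the data do not match. The recording is handled as two periods, but its adequacy is judged on a pooled count in which wake readings can stand in for sleep readings. A recording that says almost nothing about the night can therefore be accepted for a classification that draws on a wake/sleep split.

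Two things could follow. A sleep-period value would be missing or rest on a handful of readings, without the rule flagging it. And if a 24-hour average is formed by simple averaging, it would lean toward wake values. Either could alter an individual's ABPM label, including masked or white-coat hypertension. Blood pressure is among the effects named in objective 3 of the Study Summary, so the labels matter to a stated aim, though not to the primary outcome.

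**Working it through.** **Inputs from the Protocol (3.3.9 b).** 24 h of recording, one reading per 30 min, 70% minimum. The percentage is taken of scheduled readings, the natural reading of the sentence. If it means attempted readings, the rule is weaker still.

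**Assumptions, not in the Protocol.** Sleep of 7, 8 or 9 h. Wake systolic BP 115 mmHg with a nocturnal fall of 10-15%. These serve only to show a range.

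**Step 1: what the rule requires.**
- Scheduled: 24 / 0.5 = 48.
- Required: 0.70 × 48 = 33.6, rounded up to 34.
- May be missing: 48 − 34 = 14.

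**Step 2: fewest sleep readings in an accepted recording.** Formula: max(0, 34 − wake readings), with every wake reading valid.

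| Assumed sleep | Sleep readings scheduled | Wake readings scheduled | Fewest valid sleep readings |
|---|---|---|---|
| 7 h | 14 | 34 | 0 |
| 8 h | 16 | 32 | 34 − 32 = 2 |
| 9 h | 18 | 30 | 34 − 30 = 4 |

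**Step 3: cuff removed exactly at bedtime.**
- 7 h of sleep: 34/48 = 70.8%. Passes, but only if no wake reading fails.
- 8 h: 32/48 = 66.7%. Fails.
- 9 h: 30/48 = 62.5%. Fails.

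For sleep longer than about 7 h, the gap therefore concerns readings lost after the night has begun.

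**Step 4: effect on a simple 24-hour systolic mean, 8 h of sleep.** Sleep SBP is 115 × 0.90 = 103.5 mmHg (10% fall) or 115 × 0.85 = 97.75 mmHg (15% fall).

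Complete recording:
- 10%: (32 × 115 + 16 × 103.5)/48 = 111.2
- 15%: (32 × 115 + 16 × 97.75)/48 = 109.25

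All 32 wake and 2 sleep readings valid:
- 10%: (32 × 115 + 2 × 103.5)/34 = 114.3, overstated by 3.2 mmHg
- 15%: (32 × 115 + 2 × 97.75)/34 = 114.0, overstated by 4.7 mmHg

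29 of 32 wake readings valid, so 34 − 29 = 5 sleep readings are needed:
- 10%: (29 × 115 + 5 × 103.5)/34 = 113.3, overstated by 2.1 mmHg
- 15%: (29 × 115 + 5 × 97.75)/34 = 112.5, overstated by 3.2 mmHg

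(Differences are taken before rounding.)

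**Step 5: the same 70% applied within each period.** Required sleep readings: 10 of 14 (7 h), 12 of 16 (8 h), 13 of 18 (9 h). Required wake readings: 24 of 34, 23 of 32, 21 of 30. The present rule guarantees only 0, 2 and 4 sleep readings.

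**The case against.** Several objections have force.

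- **Bedtime removal.** A reader might infer that anyone who takes the cuff off at bedtime passes. Step 3 shows otherwise: the rule rejects that recording once sleep is longer than about 7 h, and at 7 h it passes only with a faultless day.
- **Size.** A reader might take 3-5 mmHg as the typical error. It is a worst case that needs every wake reading to be valid. With three wake readings lost it falls to about 2.1-3.2 mmHg, and with 27 of 32 valid an accepted recording must hold 7 sleep readings.
- **Target quantity.** The Protocol names no 24-hour, wake or sleep mean as an endpoint. If classification judged the two periods separately, the bias in a 24-hour mean would not matter. The thin sleep data still would.
- **Cause and frequency.** Nothing in the Protocol says why or how often night readings are lost, or that the loss is non-random. No share of misclassified participants can be given.
- **Comparison between arms.** The same rule applies to both arms and outcome assessors are blinded (3.3.6 d). A reader might infer a biased treatment effect, but the Protocol gives no ground for expecting night-time wear to differ by arm.
- **Place for the rule.** Per-period validity could sit in a statistical analysis plan or an ABPM manual. That is fair as to location. But the Protocol does fix an acceptance rule and calls it sufficient, so a later document would have to tighten it. The guideline is cited here for thresholds and percentiles, not for accepting recordings.

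These points limit the size and reach of the problem. They do not remove the mismatch between a pooled count and a two-period use.

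**Conclusion.** The concern holds in a limited form. As written, the rule accepts recordings with as few as 0 of 14, 2 of 16 or 4 of 18 sleep readings for assumed sleep of 7, 8 or 9 h, provided all wake readings are valid. The counts follow from the Protocol's own schedule and threshold; only sleep length is assumed. The possible overstatement of a simple 24-hour systolic mean is at most 3.2-4.7 mmHg under the stated assumptions, and less once wake readings are also lost. Its frequency cannot be judged from the Protocol.

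The consequence is confined to a secondary assessment. The primary outcome comes from client care records (3.3.9 a), and hypothesis 2 in section 1.10 concerns arterial stiffness. This is a cheap improvement to a measurement rule, not a threat to the trial's main conclusion.

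**What to change.** Replace the acceptance sentence in 3.3.9 b with wording such as: *A recording is valid for the wake period, or for the sleep period, only if at least 70% of the readings scheduled in that journal-defined period are valid. Classification on sleep or 24-hour BP requires both periods to qualify. Recordings that fail only the sleep criterion contribute wake BP only.* This also settles the denominator as scheduled readings.

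The cost is one sentence and one check at data cleaning; the journal times are already to be collected. The downside is that some recordings that now pass would no longer count for sleep or 24-hour classification. Their number cannot be estimated from the Protocol, so the count of recordings failing each criterion should be reported by arm and assessment round. Applying the Protocol's own 70% to each period is a reasonable choice rather than one the document dictates. Whichever minimum is chosen should be fixed before any ABPM recording is classified.
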